#### HEP Control

The HEP is a time- and attention-matched education control [68,69]. The HEP has been used in similar RCTs, including those involving older adults with SCD [74,81,83,92,197-201]. This active control accounts for the effect of time spent as well as feedback and support from group members and the study clinician. Participants receive lifestyle education consistent with public health recommendations and standards for health promotion (eg, physical activity, sleep, and the Mediterranean diet; Textbox 2). Participants do not learn the mindfulness or behavior modification skills unique to MHB. To control for the time and attention devoted to MHB skills, HEP participants are instructed to journal for 5 to 10 minutes per day. HEP participants wear the Garmin Vivosmart 5 but do not monitor steps and sleep or set goals (ie, these features are disabled in the Garmin Connect app).

### Data Analyses

#### Power Analysis

Consistent with the NIH Stage Model [62] and guidelines for feasibility pilot studies [76,77], the pilot RCT trial is primarily focused on feasibility benchmarks and *not* efficacy testing. With a sample size of 50 participants and assuming conservatively that the 10 feasibility criteria are independent, the study will have >80% power to confirm all benchmarks if at least 82% of the participants meet the specified benchmark for each criterion. The proposed sample size is consistent with prior similar pilot trials [83].

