**Acceptability**							
	Satisfaction	Client Satisfaction Questionnaire [108] assesses patient satisfaction with the program; percentage of participants with scores (minimum=3, maximum=12) above the scale’s midpoint		≥70%=good, ≥80%=excellent		After the intervention	
	Program attendance	Percentage of participants who attend ≥6 out of 8 sessions		≥70%=good, ≥80%=excellent		After the intervention	
	Perceived improvements	Modified Patient Global Impression of Change [109] asks participants about perceived improvements in cognitive function, lifestyle, and emotional well-being outcomes; percentage of participants who report improvement in each outcome domain (ranging from 1=*very much worse* to 7=*very much improved*)		≥70%=good, ≥80%=excellent		After the intervention and at 6-month follow-up	

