**Fidelity**							
	Therapist fidelity	Percentage of sessions in which the study clinician completed an audio recording, progress note, and checklist with 100% of the content delivered (confirmed by blinded RA independently coding a random 10% of audio-recorded sessions)		≥75%=good, 90%=excellent		Study completion	
	Study procedures	Fidelity of staff to the study procedures as calculated by the frequency of protocol deviations		<5 deviations=good, 0 deviations=excellent		Study completion	
Patient safety			Number of self-reported adverse events		Mild in ≤10% of participants=good, none=excellent		Study completion

**Table 2 table2:** Study measures and constructs. Demographic and clinical characteristics are assessed before the intervention. All other measures are assessed before the intervention, after the intervention, and at 6-month follow-up.

Measure and description		Scoring	Psychometric evidence

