#### Primary Analyses (Feasibility)

Statistical analyses will be performed in R (version 4.2.1; R Foundation for Statistical Computing) using RStudio (Posit Software, PBC) [202,203]. We will calculate frequencies and proportions to assess a priori feasibility Go–No-Go benchmarks for the feasibility, acceptability, appropriateness, credibility, satisfaction, and fidelity of the programs [64,70-74]. If these benchmarks are not met, revisions will be necessary before an efficacy trial. We will report benchmarks separately for the MHB intervention and HEP control groups.

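### The stated power above 80% to confirm all benchmarks holds only for 50 pooled participants; in an arm of about 25, the plan's own assumptions give about 50% to 62%

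*Protocol article*

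**What the plan says.** The Power Analysis section sets out its assumptions as follows: "With a sample size of 50 participants and assuming conservatively that the 10 feasibility criteria are independent". On that basis it states that "the study will have >80% power to confirm all benchmarks if at least 82% of the participants meet the specified benchmark for each criterion".

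The Objectives section gives the primary aim as assessing MHB against established Go–No-Go benchmarks. The Randomization section allocates 1:1 in blocks of four, so 50 participants yield about 25 per arm. The Primary Analyses (Feasibility) section says: "We will report benchmarks separately for the MHB intervention and HEP control groups". It adds that unmet benchmarks will require revisions before an efficacy trial. The Abstract likewise describes the proportions of MHB and HEP participants meeting each benchmark. No pooled evaluation is described.

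Table 1 lists ten rows under its four named constructs: four for feasibility, three for acceptability, one for appropriateness and two for fidelity. Most have a lower threshold of 70%; therapist fidelity has 75%. Perceived improvement is scored as the "percentage of participants who report improvement in each outcome domain", and the row names three domains.

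**The concern.** The power statement and the analysis use different units. The calculation gives each criterion a denominator of 50. The primary aim and the reporting plan point to one arm, with half that number. With 25 people an observed proportion varies more around a true 82%, so the chance that at least one of several criteria falls below 70% rises sharply.

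Three of the ten rows also do not fit a model in which a share of enrolled participants meets each criterion. Enrolment is counted among all those contacted, therapist fidelity is counted over sessions, and study procedures are a count of deviations.

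The benchmarks are the primary outcome and decide whether the program goes forward unrevised. A reader who takes the stated power at face value will believe that a program succeeding at 82% on every criterion is very likely to clear them all. For one arm, on the plan's own assumptions, that is not so.

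**Working it through.** **Inputs.** From Power Analysis: N = 50, ten independent criteria, true rate 0.82 on each. From Table 1: lower threshold 70% (therapist fidelity 75%). From Randomization: 1:1, so n = 25 per arm. No significance test is planned; observed proportions are compared with thresholds.

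**Formula.** For one criterion, power = P(X ≥ r), with X ~ Binomial(n, 0.82) and r the smallest whole number not below threshold × n. For k independent criteria, joint power is the product of the single powers.

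**The plan's figure, pooled n = 50.**
- 70% threshold: P(X ≥ 35) = 0.988. Ten criteria: 0.988^10 = 0.886 (unrounded inputs).
- 75% threshold: P(X ≥ 38) = 0.898. Nine at 70% and one at 75%: 0.988^9 × 0.898 = 0.805.

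Both agree with the statement of more than 80%.

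**One arm, n = 25.** P(X ≥ 18) = 0.934.

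| Criteria counted | Joint power at 82% | True rate needed for 80% |
|---|---|---|
| 10, all as arm-level proportions at 70% | 0.934^10 = 0.505 | about 85.4% |
| 7 participant-proportion rows | 0.934^7 = 0.62 | about 84.4% |
| 9 (the 7 rows, perceived improvement as three domains) | 0.934^9 = 0.54 | about 85.1% |

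The seven rows are outcome assessments, watch wear, daily surveys, satisfaction, attendance, perceived improvement, and credibility and expectancy. With ten criteria and one of them at 75%, where P(X ≥ 19) = 0.851, the figure is 0.934^9 × 0.851 = 0.46.

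**Sensitivity to arm size.** For ten criteria at 70%, an arm of 24 (r = 17) gives 0.58 and an arm of 26 (r = 19) gives 0.43. The spread comes largely from rounding 70% to a whole number of people.

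**Sensitivity to correlation.** If the criteria at 70% were perfectly correlated, joint power would equal the single-criterion value, 0.934.

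**Mixed unit.** Suppose the three procedures shared by both arms (outcome assessments, watch, daily surveys) are judged on 50, and the four program-specific rows (satisfaction, attendance, perceived improvement, credibility) on MHB alone. Then power is 0.988^3 × 0.934^4 = 0.73. With perceived improvement as three domains it is 0.988^3 × 0.934^6 = 0.64.

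**The case against.** The strongest reply is that the arithmetic is sound for the unit it names: the section speaks of the study and of 50 participants. The analysis section says that benchmarks will be reported by arm, not that they will be judged by arm, and enrolment among those contacted precedes randomization and cannot be split by arm. This stands to the extent that a per-arm decision is an inference. It is a firm one, because the primary aim concerns MHB and no pooled evaluation is described. If a pooled decision is meant, the text needs to say so.

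Independence is also the plan's declared conservative case. Attendance, watch wear, surveys and satisfaction come from the same people, so positive correlation is plausible. The per-arm figures are therefore floors. A reader might infer that MHB faces an even chance of missing a benchmark; the documents support that only under independence with all ten criteria counted at arm level.

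Three further readings are not supported:
- A reader might count eleven rows in Table 1 and conclude that ten is wrong. The four named constructs contain exactly ten rows, and patient safety stands outside them.
- For the same reason the adverse-event row ("Mild in ≤10% of participants=good, none=excellent") should not be used to attack the power figure.
- A reader might call this the sole justification of the sample size. The section also cites guidelines for pilot studies and consistency with similar trials.

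Finally, this is a feasibility pilot with descriptive benchmarks. That limits the consequences, but does not make a pooled figure apply to one arm.

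**Conclusion.** The point holds as a mismatch of unit, not as an arithmetic error. The claim of more than 80% is correct for 50 pooled participants (0.886, or 0.805 with one threshold at 75%). It does not carry over to an arm of 25. There, at a true rate of 82% and under independence, power is about 50% for ten criteria, 62% for the seven participant-proportion rows and 54% if perceived improvement counts as three domains. None of these reaches 80%.

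The result rests on the lower Table 1 thresholds, arms of about 25, no dropout and the plan's independence assumption. Positive correlation would raise the per-arm values, to no more than 93%. It also rests on reading the Go–No-Go decision as one about MHB, which the primary aim supports but the analysis section does not spell out.

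**What to change.** State in the Power Analysis and Primary Analyses (Feasibility) sections the unit on which Go–No-Go is decided, and give the power for that unit:

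- **MHB alone:** about 62% for the seven participant-level criteria at 82%, with 80% reached at a true rate of about 84.4%. If ten criteria are kept, about 50%, with 80% reached at about 85.4%.
- **Mixed unit:** shared procedures on the pooled 50 and the four program-specific criteria on MHB n = 25, about 73% (64% with three perceived-improvement domains).
- **Pooled 50 throughout:** say so explicitly and reconcile it with the primary aim and the reporting by arm.

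In each case list the criteria counted, say whether perceived improvement is one criterion or three, and take the enrolment, therapist-fidelity and deviation rows out of the participant-proportion calculation. Those rows remain benchmarks, judged on their own denominators. Exact confidence intervals beside each proportion would be a useful option but are not required.

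The cost is wording only. The stated power becomes less favourable unless a pooled decision is declared, and no extra participants are needed.

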#### Primary Analyses (Feasibility)

Statistical analyses will be performed in R (version 4.2.1; R Foundation for Statistical Computing) using RStudio (Posit Software, PBC) [202,203]. We will calculate frequencies and proportions to assess a priori feasibility Go–No-Go benchmarks for the feasibility, acceptability, appropriateness, credibility, satisfaction, and fidelity of the programs [64,70-74]. If these benchmarks are not met, revisions will be necessary before an efficacy trial. We will report benchmarks separately for the MHB intervention and HEP control groups.

#### Exploratory Analyses

Consistent with the Science of Behavior Change framework [189], we will test preliminary improvements and explore mechanisms to guide intervention refinements before efficacy testing. For each measure, we will report descriptive statistics, paired samples 2-tailed *t* tests, and Cohen *d* effect sizes (small=0.2, medium=0.5, and large=0.8) [204] with 95% CIs and minimal clinically important difference where available. We will analyze the MHB and HEP groups separately. We will explore associations between hypothesized mechanisms and outcomes to gauge the evidence of engagement in the targets of the MHB intervention. Finally, we will examine adherence and person-specific patterns of intensive longitudinal data (Garmin Vivosmart 5, multiday BRANCH tests, and daily surveys) during the RCT.

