**Feasibility**							
	Recruitment and enrollment	Percentage of individuals who participate and enroll from the total contacted		≥70%=good, ≥80%=excellent		Before the intervention	
	Outcome assessments	Percentage of participants with no missing outcome assessment data		≥70%=good, ≥80%=excellent		Before the intervention, after the intervention, and at 6-month follow-up	
	Garmin Vivosmart 5 watch	Percentage of participants who wore the watch at least 5 out of 7 days per week [106,107] for at least 10 hours a day [71]		≥70%=good, ≥80%=excellent		After the intervention	
	Daily surveys	Percentage of participants who completed at least 5 out of 7 daily surveys during the program		≥70%=good, ≥80%=excellent		After the intervention	

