Garmin Vivosmart 5 adherence is defined as ≥10 hours of valid wear time based on prior research [180-183]. Wear time is calculated in relation to heart rate by Fitabase [184]. The RA monitors Fitabase and contacts participants after 48 hours of Garmin Vivosmart 5 nonadherence to provide technical support. We estimate a truncated average 7-day step count and sleep data for each participant, measured by the Garmin Vivosmart 5 before the intervention, after the intervention, and at the 6-month follow-up, using an established protocol [71,92,96]. We exclude nonadherent or invalid days of wear as well as the highest and lowest values to reduce the influence of outliers. A minimum of 3 valid days of wear at each time point is required to calculate the averages. Sleep metrics include total hours asleep and sleep efficiency (the ratio of time asleep to time spent in bed) using guidelines for older adults [185]. We visually inspect sleep-wake patterns during the day to exclude naps from the sleep calculations [186].

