##### Randomization

One week before the first session of MHB or the HEP, the RA randomizes participants to receive either 8 weeks of the MHB intervention or the HEP education control. Randomization follows a 1:1 ratio using permuted blocks of size 4. To maintain blinding of group assignments, participants are informed that they can participate in 1 of 2 programs: MHB 1 (active intervention [MHB]) or MHB 2 (control [HEP]). To reduce contamination, we ask participants not to share specific information discussed in the group (eg, skills learned and topics discussed) with anyone for the duration of the study. All participants will receive both electronic and paper copies of their assigned treatment manual.

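### The planned paired t tests and Cohen d values use complete pairs only; if follow-up data are missing they discard usable data and may be biased in either direction

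*Protocol article*

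**What the plan says.** Under Exploratory Analyses the article fixes the method for the secondary and mechanism measures: "For each measure, we will report descriptive statistics, paired samples 2-tailed *t* tests, and Cohen *d* effect sizes", with 95% CIs and a comparison with the minimal clinically important difference where one exists. The two arms are analysed separately. The Abstract names the same method for the secondary outcomes. Measures are taken before the program, after it and at 6 months.

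For steps and sleep, the section on the Garmin watch adds a further condition: "A minimum of 3 valid days of wear at each time point is required to calculate the averages". This applies to the watch averages only.

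Missing outcome data are themselves a primary feasibility measure. Table 1 tracks "Percentage of participants with no missing outcome assessment data" at all three time points, graded "≥70%=good, ≥80%=excellent". Under Objectives, the results are said to inform a later efficacy trial.

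**The concern.** The secondary aim concerns improvement among people randomized to a program. A paired t test answers a narrower question: how much did participants with both values of this pair change? Someone with baseline and post-program values but no 6-month value contributes nothing to the 6-month estimate, although the post-program value says something about the missing one. Someone with baseline and 6-month values only contributes nothing to the post-program estimate.

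In a behavior-change program, not returning for assessment or not wearing an activity watch may well be related to how much the person changed. If so, the complete-pair effect differs from the effect in everyone assigned. At stake are the effect sizes and the comparisons with the minimal clinically important difference that readers will take from this pilot.

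The article gives some reason to expect gaps at follow-up. Payment rises to US $90 at 6 months to protect retention. The US $40 wear bonus covers only the period before the program, whereas the 3-day rule applies at every time point. No 6-month data are reported yet.

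**Working it through.** **1. The plan's own figure, and what 82% means.** The Power Analysis section has N = 50, 10 criteria taken as independent, and power above 80% "if at least 82% of the participants meet the specified benchmark for each criterion". With the 70% threshold (at least 35 of 50), P(X ≥ 35 | 50, 0.82) = 0.988 and 0.988^10 = 0.886. The claim reproduces. The 82% is thus a condition in a power statement about benchmarks, not a forecast of missing data. The article states no expected missing rate and no assumed effect size, so every missingness figure below is an assumption.

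**2. Deterministic illustration.** Let m be the share of pairs missing and r the change in the missing relative to those observed. Then complete-pair mean / all-randomized mean = 1 / [(1 − m) + m·r].

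| m | r = 0 | r = 0.5 | r = 1 | r = 1.5 |
|---|---|---|---|---|
| 0.18 | 1/0.82 = 1.22 | 1/0.91 = 1.10 | 1.00 | 1/1.09 = 0.92 |
| 0.30 | 1/0.70 = 1.43 | 1/0.85 = 1.18 | 1.00 | 1/1.15 = 0.87 |

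The values of m are borrowed from the 82% condition and the 70% threshold only to set a range. They are high, because the Table 1 criterion fails a participant who lacks anything at any visit, while that person still contributes to most pairs.

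**3. Missingness that depends on the change itself.** Simulated change scores with true d = 0.50 and SD 1, with the log-odds of being missing shifting per SD of change:

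| Missing | Unrelated | Poor responders lost (0.5 to 1.0 per SD) | Good responders lost (0.5 per SD) |
|---|---|---|---|
| 5% | 0.50 | 0.53–0.56 | 0.48 |
| 10% | 0.50 | 0.55–0.61 | 0.45 |
| 20% | 0.50 | 0.61–0.71 | 0.41 |
| 30% | 0.50 | 0.66–0.81 | 0.36 |

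**4. Scale against sampling error.** With 25 per arm and d = 0.5, SE = √(1/25 + 0.5²/50) = √0.045 = 0.212, so the 95% CI is 0.5 ± 0.42, or 0.08 to 0.92. At 5% to 10% missing, sampling error dominates. At 20% to 30% the shift can reach 0.11 to 0.31 when poor responders are lost. The interval does not reflect that shift.

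**5. What a mixed model gains.** With 6-month dropout depending on the observed post-program change (10% to 30% missing, n = 25, true change 0.50), the paired estimate was 0.54 to 0.61 under the stronger dependence simulated. A likelihood estimate using all three time points was 0.50, with similar spread.

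**6. What it does not gain.** With 25 per arm and 18% having zero change and no follow-up value (0.5 SD change in the rest; baseline to follow-up correlation 0.5 or 0.7), mean change was 0.41 in all, 0.50 in completers and 0.50 from a likelihood estimate using everyone's baseline. A model that assumes missing at random cannot repair that case. Setting the missing to no change gives 0.82 × 0.50 = 0.41.

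**7. Data so far.** Dropout is 0 of 21, and 9 of 9 in cohort 1 have post-program assessments. The exact two-sided 95% upper limit for 0/21 is 1 − 0.025^(1/21) = 16%. Garmin adherence is 128/147 weeks, so 19/147 = 13% of weeks were nonadherent.

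**The case against.** The strongest objection is that the article names a test and says nothing about analysis sets or imputation, which are commonly left to a full protocol or analysis plan not shown here. That is right as far as it goes: the absence of a missing-data section is not the point. The point is the method that is stated. Unless values are imputed, a paired t test is a complete-pair analysis, and the 3-day rule is an explicit further exclusion.

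A second objection is that retention is excellent, that staff contact participants after 48 hours without wear, and that completeness will be reported by arm as a primary benchmark. This stands. It lowers the likely size of the problem, but it does not settle 6-month retention.

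A third is that a mixed model returns the completer answer when missingness depends on unseen change. This also stands, and it is why a sensitivity analysis has to accompany the model.

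Two stronger readings should be resisted. A reader might infer that the valid-days rule restricts every measure. It covers only Garmin steps and sleep, and is looser than the 5-of-7-day wear benchmark. A reader might also infer that only people who stayed engaged are analysed. Nothing makes attendance or practice a condition of analysis, so someone who skips sessions but completes assessments is included.

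**Conclusion.** The concern holds in a limited form. As stated, each within-arm effect describes participants with both values of the pair, and for Garmin outcomes those with enough valid wear at both time points. If data are missing, usable intermediate data are discarded and the effect may be biased in either direction, upward if poor responders are lost. If data are complete, or missingness is unrelated to change, there is no bias. The +10% to +43% figures are illustrations that assume 18% to 30% of pairs missing and a relative change of 0 to 0.5 in those missing; they are not predictions.

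Two further inferences are not supported. One is that the effects are likely too large: the direction depends on why data are missing, and no dropout has been observed. The other is that a later trial would be undersized, for example at 0.82² = 67% of the required number. The article describes these analyses as exploratory and says only that results will inform the efficacy trial. It does not say that d will size that trial, and the planned d values are within-arm whereas the later comparison is between arms.

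The change is still worth making, because it costs little and recovers information if 6-month data are incomplete.

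**What to change.** - For each measure, estimate the pre-to-post and pre-to-6-month changes in each arm, with standardized effects and 95% CIs, from one repeated-measures mixed model. Use all randomized participants and all three time points, with time as categorical and REML estimation.
- Because this model assumes missing at random, add one sensitivity analysis that sets missing follow-up values to no change from baseline. For Garmin outcomes, count fewer than 3 valid wear days as missing.
- Keep the paired t test, labelled as a complete-pair analysis, with the number of participants contributing to each pair.

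The cost is a change of analysis wording and slightly more analysis work in R, with no new data or participants. Reported effects may turn out smaller.

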**Exclusion criteria and brief rationales**
Mild cognitive impairment, AD/ADRD, or other neurodegenerative disease: study confound (intervention targets early AD/ADRD risk; ability to participate meaningfully)Psychotropic medication (eg, antidepressant) change in <3 months: study confoundPsychosis, uncontrolled bipolar disorder, or uncontrolled substance dependence or abuse: study confound (safety of participants; treatment confound; can affect participants’ answers)Current self-report of suicidal ideation: participant safetySerious medical illness expected to worsen in 6 months (eg, cancer): study confound (serious medical illness may act as a third variable)Use of an activity watch to track physical activity or sleep in <3 months and unwillingness to stop using it for the duration of the program: treatment confoundMindfulness practice lasting >45 minutes per week or cognitive behavioral therapy in <3 months: treatment confoundSelf-reported step count >5000 per day or ≥30 minutes of exercise per day: study population (intervention targets increased activity among sedentary older adults)

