**Alcohol and tobacco use**			
	PROMIS Alcohol Use [137]*,* a 7-item self-report of at-risk drinking	5-point scale ranging from 1=*never* to 5=*almost always*; higher T-scores indicate greater problematic alcohol use	High convergent validity [137] and modest test-retest reliability [138]
	CDC^f^ Behavioral Risk Factor Surveillance System questionnaire concerning tobacco use [139]*,* a 2-item self-report of tobacco use history and current frequency of use of 6 common tobacco products	5-point scale ranging from 1=*less than once a month* to 5=*daily or almost daily*; higher scores indicate greater tobacco use	—

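### Tobacco use is to be summarized by a whole-arm paired t test and labelled Cohen d, which with few users would mostly show how many people changed and not by how much

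*Protocol article*

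**What the plan says.** The Exploratory Analyses section applies one recipe to all outcomes: "For each measure, we will report descriptive statistics, paired samples 2-tailed" t tests, with Cohen d described as "effect sizes (small=0.2, medium=0.5, and large=0.8", reported "with 95% CIs and minimal clinically important difference where available". The arms are kept apart: "We will analyze the MHB and HEP groups separately". No measure is exempted.

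Tobacco and alcohol use are among these measures. The abstract lists both under the secondary lifestyle outcomes, and Table 2 gives the instruments:
- **Tobacco:** a two-item questionnaire covering history and current frequency for six products, on a scale from 1 to 5, where "higher scores indicate greater tobacco use". The lowest point is use less often than monthly, and Table 2 shows no value for someone who does not use tobacco.
- **Alcohol:** a seven-item T-score, where "higher T-scores indicate greater problematic alcohol use".

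Textbox 1 has no criterion requiring use of either substance. The only related criterion excludes "uncontrolled substance dependence or abuse". The MHB Intervention section names tobacco cessation among the targeted behaviors, and MHB session 7 covers alcohol, tobacco and urges.

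**The concern.** Only a tobacco user can stop or cut down. A non-user can contribute no improvement, and if scored at all contributes a change of zero unless he or she starts. When most differences are zero, the mean and the SD of the differences are both driven by the few people who changed. Their ratio then says more about how many changed than about how far they moved.

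The target for tobacco is cessation, which is an event. A mean frequency change over the whole arm, graded against generic cut-offs, does not measure it. Complete success among a handful of smokers could be graded as small, and one person's change could also earn that label. The results are meant to guide refinement of the program and inform the later efficacy trial, so a misread label could affect what is said about the tobacco component.

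**Working it through.** **Plan's own figure.** The article gives no expected d, power or prevalence for tobacco or alcohol, so there is nothing on this point to reproduce. Its one power statement, "With a sample size of 50 participants and assuming conservatively that the 10 feasibility criteria are independent", concerns the feasibility benchmarks and is used here only for N = 50.

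**Inputs from the article.** N = 50 (Power Analysis), 1:1 allocation (Randomization) and analysis by arm (Exploratory Analyses) give n = 25 per arm if everyone completes.

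**Assumptions.** Non-users score no change; k people change by the same amount c; d is the mean difference divided by the SD of the differences.

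**Formula.** Mean = kc/n. Variance = [kc² − (kc)²/n]/(n − 1) = c²k(n − k)/[n(n − 1)]. Hence

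d = √{k(n − 1)/[n(n − k)]}

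The amount c cancels. For k = 1 this is 1/√n = 1/5 = 0.20.

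| Changers of 25 | d | p (paired t) | 95% CI for d |
|---|---|---|---|
| 1 | √(24/600) = 0.20 | 0.33 | −0.20 to 0.59 |
| 2 | √(48/575) = 0.29 | 0.16 | −0.11 to 0.69 |
| 3 | √(72/550) = 0.36 | 0.08 | −0.05 to 0.76 |
| 4 | √(96/525) = 0.43 | 0.04 | 0.01 to 0.83 |
| 5 | √(120/500) = 0.49 | 0.02 | 0.07 to 0.90 |

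Ten equal changers give √(240/375) = 0.80. If nobody changes, d is 0/0.

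**Without equal changes.** Let d among users be 0.8 (assumed), with everyone else at zero and a fraction f of the arm using. The whole-arm d is 0.8f/√[1.64f − (0.8f)²]. With 1, 3, 5, 10 and 15 users of 25 this is 0.13, 0.22, 0.29, 0.43 and 0.55. The same effect among users is thus graded differently according to how many users there are.

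**How many users?** This is unknown. Assuming 5%, 10% or 20% use tobacco, an arm of 25 has on average 1.3, 2.5 or 5 users. The chance of none is 0.95²⁵ = 28%, 0.90²⁵ = 7% or 0.80²⁵ = 0.4%.

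**Sensitivity to the definition of d.** Put non-users at 0 and users at 5, let one person change by 1, 2 or 5 points, and divide by the baseline SD.
- With one user in the arm, d = 0.04, 0.08, 0.20.
- With five users, d = 0.02, 0.04, 0.10.

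Here d does vary with the amount. Full cessation is the exception. If all users share one baseline level and all stop, each difference equals the baseline score in size. The baseline SD and the SD of the differences then coincide, and d is again 0.20, 0.29 or 0.36 for one, two or three quitters.

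**Sensitivity to the pattern and n.** Two equal and opposite changes give d = 0. Changes of 1 and 4 points in two people give 0.24, against 0.29 for equal changes. One changer gives 0.22 with 20 completers.

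**The case against.** The strongest reply has four parts.

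- **The result depends on the definition.** The article says only Cohen d. That d is independent of the amount holds for the SD of the differences with equal changes. This stands, with the cessation case above as a partial exception.
- **The floor is assumed.** No use rates are reported, and ordinary smokers and drinkers are eligible. Few users is a reasonable working assumption for tobacco. It is weak for alcohol, because nothing shows that drinkers sit at the minimum of a seven-item T-score. If tobacco non-users receive no frequency score, the paired test is already confined to users. This stands too.
- **Safeguards exist.** Descriptive statistics and 95% CIs are promised. For one changer, p = 0.33 and the interval from −0.20 to 0.59 would mislead nobody. That limits the harm, but an interval around d does not tell the reader how many users there were or how many stopped.
- **The analysis is exploratory.** Primary Analyses ties the need for revision to the feasibility benchmarks only. This also stands.

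A reader might infer that d simply counts the users enrolled, or that it carries no information about how much they changed. Neither is supported: users who do not change add nothing to the mean, and unequal or opposite changes alter d. A reader might also infer that alcohol should be tested only in people above the scale minimum at baseline. That would select on the baseline score of a within-arm pre-post comparison, so regression to the mean would favor apparent improvement in both arms.

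**Conclusion.** The point holds for tobacco in limited form. The plan fixes a whole-arm paired t test and a labelled d for an outcome whose stated target is cessation, in a sample not selected for use. If users are few, non-users are scored as unchanged and d uses the SD of the differences, then one to five equal changers among 25 completers give d from 0.20 to 0.49 regardless of amount. That spans the label for small and nearly reaches medium. With another denominator or unequal changes, the size of change does enter.

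For alcohol, the article gives no ground to call the planned analysis wrong; it needs only a supplementary description. The point is minor: it concerns how an exploratory result is reported and leaves the go/no-go decision unaffected.

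**What to change.** - **Tobacco:** replace the paired t test and labelled d. Per arm and time point, report the number of baseline users, the number of these who stopped or reduced with an exact 95% CI, and the number of baseline non-users who started.
- **Alcohol:** keep the planned whole-arm analysis. Add the number at the scale minimum at baseline and a descriptive summary of change among those above it. Do not test that subgroup.
- **All measures:** state which Cohen d is used.

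The cost is a few sentences of analysis wording, since the items are already collected. The downside is that the tobacco denominators will be small and the intervals wide. Even if three of three users stopped, the exact lower limit would be 0.025^(1/3) = 0.29, so the interval runs from 29% to 100%.
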